# **1. INTRODUCTION**

## **1.1 Background**

### **1.1.1 Hepatocellular Carcinoma**

Hepatocellular carcinoma (HCC) is one of the commonest solid malignancies in Asia Pacific region, primarily because of high incidence of hepatitis B infection in this locality. Resection or liver transplantation (LT) is the standard treatment for operable/resectable disease. However the waiting time for LT can be very long, especially in countries/regions where organ shortage is a serious problem. Bridging therapy like transarterial chemoembolization (TACE), radiofrequency ablation or more recently transarterial radioembolization have been investigated and evaluated in HCC patients before LT. Stereotactic body radiation therapy (SBRT) has also been explored and evaluated in this study. However so far, there has been no prospective trial on SBRT as bridging therapy before LT, though retrospective studies revealed promising tumor response and safety profiles. There are no studies on using magnetic resonance imaging (MRI) and dual-tracer PET-CT scan in HCC diagnosis and treatment monitoring in this setting.

### **1.1.2 Stereostactic Body Radiation Therapy**

Stereotactic body radiation therapy (SBRT), with the use of highly conformal and precision radiation techniques with real-time tracing of patient and tumor position so as to offer a high radiation dose to the tumors while sparing the adjacent critical organs from necessary radiation.

### **1.1.3 Magnetic resonance imaging (MRI) with gadoxetate disodium**

Contrast-enhanced triphasic computed tomography (CT) scan has been regarded as the standard imaging tool in HCC diagnosis and treatment monitoring. MRI with gadolinium contrast injection demonstrated comparable sensitivity and specificity with contrast-enhanced computed tomography for HCC lesions > 2cm. The addition of liver specific contrast gadoxetate disodium further improves detection of 1-2cm tumors, demonstrating 92.1% accuracy based on the Milan and UNOS guidelines. Two recent meta-analysis revealed that gadoxetate disodium-enhanced MRI demonstrated higher sensitivity and diagnostic accuracy than contrast-enhanced CT scan, especially for lesions < 2cm.

### **1.1.4 Dual-tracer positron-emission tomography with integrated computed tomography (PET-CT)**

PET-CT with 18F-fluorodeoxyglucose (FDG) has also been evaluated in HCC diagnosis and surveillance after treatment. However, FDG is just able to detect poorly differentiated HCC only. Dual-tracer (11C-acetate [ACC] and 18F-fluorodeoxyglucose [FDG]) positron-emission tomography with integrated CT (PET-CT) was proven more sensitive and specific than FDG-alone PET-CT in HCC diagnosis and surveillance. In particular, dual-tracer PET-CT was found superior than contrast-enhanced CT scan in diagnosing and selecting

patients for LT, so that the liver grafts were given only to those who really fulfilled the LT criteria.

### **1.1.5 Rationale for conducting this study**

In view of the above with, we are proposing a phase 2, single-arm study on SBRT as a bridging therapy before LT for HCC patients. MRI with gadoxetate disodium and dual-tracer PET-CT scan will be used as HCC diagnosis as well as treatment response evaluation following SBRT until LT is done or when progressive disease is documented. By doing so, it is hoped that these two imaging modalities will help identify those who truly fulfilled LT criteria so that LT will only be performed to those who are accurately and reliably diagnosed with the most contemporary imaging techniques.

## **1.2 Research hypothesis**

1. We hypothesize that SBRT as bridging therapy before LT can achieve an objective response of 85%
2. We hypothesize that SBRT as bridging therapy
3. We hypothesize that SBRT is safe and effective in achieving a promising objective response and local control, rendering patients suitable for LT
4. We hypothesize that dual-tracer PET-CT and MRI with gadoxetate disodium can accurately diagnose and stage HCC patients to meet LT criteria and facilitate subsequent SBRT planning and monitor tumor response after SBRT

### **1.3.1 Potential benefits of this study**

We expect that SBRT as bridging therapy can produce an 85% objective response rate, so that enough time is allowed for the patients to wait for LT. Besides, use of dual-tracer PET-CT and magnetic resonance imaging with gadoxetate disodium can provide more accurate diagnosis, staging for HCC and treatment response monitoring after SBRT so that LT will be allocated to those who fulfills the LT criteria.

### **1.3.2 Potential risks of this study**

Patients undergoing SBRT may have a risk of radiation-induced liver injury (RILD), which depends on the radiation dose and fractionation to the liver. Classic RILD is a syndrome occurring most often within 2 months following radiation therapy, consisting of anicteric hepatomegaly and elevation of liver enzymes (ALP>AST). Treatment for RILD is usually symptomatic though it may progress to liver failure, despite maximal supportive care. Classic RILD is uncommon in modern radiation therapy series like SBRT, when the dose to the liver can be kept below recommended levels. Non-classic RILD, referring to any decline in liver function or liver toxicity, excluding classic RILD (e.g. elevated transaminases or reduction of Child-Pugh score) is more common in HCC patients treated with RT. It is more likely in patients with a higher Child-Pugh score at baseline and in those with more advanced tumors requiring a larger volume of liver to be irradiated.

## **2. STUDY OBJECTIVES**

## **2.1 Primary Objectives**

- Progression-free survival (PFS), calculated from start of SBRT to the date of radiologically confirmed progressive disease based on RECIST, mRECIST, and PERCIST or death from any cause
- Best objective response as defined by RECIST 1.1, mRECIST, and PERCIST

## **2.2 Secondary Objectives**

- Local control rate as defined by RECIST 1.1, mRECIST, and PERCIST
- Overall survival (OS), calculated from start of treatment to the date of death from any cause
- Safety and toxicity profiles as determined by Common Terminology Criteria for Adverse Events (CTCAE) version 4.0

## **2.3 Study Design**

This study is a prospective phase II, single-arm study assessing the efficacy and safety of SBRT as bridging therapy in HCC patients who are awaiting LT.

## **2.4 Study Participants**

A total of 35 patients will be screened and 28 patients will be recruited and analysed to estimate the potential benefits and safety profiles of SBRT as bridging therapy before LT.

# **3. ELIGIBILITY CRITERIA**

## **3.1 Inclusion Criteria**

1. Patients must have histologically or radiologically confirmed HCC not amenable to curative resection. For radiological diagnosis of HCC, a contrast-enhanced computed tomography or magnetic resonance imaging is mandatory to demonstrate the early arterial enhancement in arterial phase and contrast washout in the porto-venous phase on the imaging.
2. Capable of giving signed informed consent which includes compliance with the requirements and restrictions listed in the informed consent form (ICF) and in this protocol. Written informed consent and any locally required authorization (e.g. Health Insurance Portability and Accountability Act in the US, European Union [EU] Data Privacy Directive in the EU) obtained from the patient/legal representative prior to performing any protocol-related procedures, including screening evaluations.

- 191
- 192 3. HCC lesions within University of California, San Francisco (UCSF) criteria for LT
- 193 (solitary tumor  $\leq 6.5\text{cm}$ , up to 3 tumors with none  $> 4.5\text{cm}$ , and total tumor diameter
- 194  $\leq 8\text{cm}$ ).
- 195
- 196 4. Be  $\geq 18$  years of age on day of signing informed consent.
- 197
- 198 5. Have a performance status of 0 to 2 on the Eastern Cooperative Oncology Group
- 199 (ECOG) Performance Scale.
- 200 6. A stage C or earlier HCC based on Barcelona Clinic Liver Cancer (BCLC) staging
- 201 system.
- 202 7. A Child-Pugh score of B8 or less.
- 203
- 204 8. Demonstrate adequate organ function as defined in Inclusion Criteria 7, all screening
- 205 labs should be performed 28 days prior to study registration up to the first dose of
- 206 study drug.
- 207
- 208 9. Adequate serum hematological functions defined as:
- 209 - Absolute neutrophil count (ANC)  $\geq 1.0 \times 10^9/\text{l}$
- 210 - Platelet  $\geq 20 \times 10^9/\text{l}$
- 211 - Hemoglobin  $\geq 8 \text{ g/dl}$
- 212 Adequate serum biochemistry functions defined as:
- 213 - Serum bilirubin  $\leq 5.0 \times$  institutional upper limit of normal (ULN). <<This will
- 214 not apply to patients with confirmed Gilbert's syndrome (persistent or recurrent
- 215 hyperbilirubinemia that is predominantly unconjugated in the absence of hemolysis
- 216 or hepatic pathology), who will be allowed only in consultation with their
- 217 physician.>>
- 218 - AST (SGOT)/ALT (SGPT)  $\leq 6.0 \times$  institutional upper limit of normal unless liver
- 219 metastases are present, in which case it must be  $\leq 6.0 \times \text{ULN}$ .
- 220 - Measured creatinine clearance (CL)  $> 40 \text{ ml/min}$  or Calculated creatinine CL  $> 40$
- 221 mL/min by the Cockcroft-Gault formula (Cockcroft and Gault 1976) or by 24-
- 222 hour urine collection for determination of creatinine clearance:

Males:

$$\text{Creatinine CL (mL/min)} = \frac{\text{Weight (kg)} \times (140 - \text{Age})}{72 \times \text{serum creatinine (mg/dL)}}$$

Females:

$$\text{Creatinine CL (mL/min)} = \frac{\text{Weight (kg)} \times (140 - \text{Age})}{72 \times \text{serum creatinine (mg/dL)}} \times 0.85$$

223

224 10. International Normalized Ratio (INR) or Prothrombin Time (PT)  $\leq 2.0 \times \text{ULN}$  unless  
225 subject is receiving anticoagulant therapy as long as PT or PTT is within therapeutic  
226 range of intended use of anticoagulants. Activated Partial Thromboplastin Time  
227 (aPTT)  $\leq 2.0 \times \text{ULN}$  unless subject is receiving anticoagulant therapy as long as PT  
228 or PTT is within therapeutic range of intended use of anticoagulants.

229

230 11. Female subject of childbearing potential should have a negative urine or serum  
231 pregnancy within 24 hours of study enrollment up to administration of the dose of  
232 study drug. If the urine test is positive or cannot be confirmed as negative, a serum  
233 pregnancy test will be required.

234

235 12. Female subjects of childbearing potential should be willing to use 2 methods of birth  
236 control or be surgically sterile, or abstain from heterosexual activity for the course of  
237 the study through 31 weeks after the last dose of study medication. Subjects of  
238 childbearing potential are those who have not been surgically sterilized or have not  
239 been free from menses for  $> 1$  year. The following age-specific requirements apply:

240

241 - Women  $< 50$  years of age would be considered post-menopausal if they  
242 have been amenorrheic for 12 months or more following cessation of  
243 exogenous hormonal treatments and if they have luteinizing hormone and  
244 follicle-stimulating hormone levels in the post-menopausal range for the  
245 institution or underwent surgical sterilization (bilateral oophorectomy or  
246 hysterectomy).

247

248 - Women  $\geq 50$  years of age would be considered post-menopausal if they  
249 have been amenorrheic for 12 months or more following cessation of all  
250 exogenous hormonal treatments, had radiation-induced menopause with  
251 last menses  $> 1$  year ago, had chemotherapy-induced menopause with last  
252 menses  $> 1$  year ago, or underwent surgical sterilization (bilateral  
253 oophorectomy, bilateral salpingectomy or hysterectomy).

254

255 13. Male subjects should agree to use an adequate method of contraception starting with  
256 the first dose of study therapy through 31 weeks after the last dose of study therapy.

257

14. Patient is willing and able to comply with the protocol for the duration of the study including undergoing treatment and scheduled visits and examinations including follow up.

15. Must have a life expectancy of at least 12 weeks.

### **3.2 Exclusion Criteria**

1. Has received any form of tumor resection of HCC.
2. Has received prior locoregional therapy including but not limited to radiofrequency ablation, microwave ablation, ethanol injection, transarterial chemoembolization and transarterial radioembolization.
3. Is currently participating in or has participated in a study of an investigational agent or using an investigational treatment/device within 4 weeks of the first dose of treatment or 5 half-lives, whichever is shorter.
4. Has a diagnosis of severe active scleroderma, lupus, other rheumatologic or autoimmune disease within the past 3 months before study recruitment. Patients with a documented history of clinically severe autoimmune disease or a syndrome requiring systemic steroids or immunosuppressive agents will not be allowed on this study. Subjects with vitiligo or resolved childhood asthma/atopy are an exception to this rule. Subjects that require intermittent use of bronchodilators or local steroid injections are not excluded from the study. Subjects with hypothyroidism stable on hormone replacement are not excluded from this study.
5. Has had a prior monoclonal antibody, immunotherapy or immune checkpoint inhibitors before recruitment into this study.
6. Has had prior chemotherapy or targeted small molecule therapy (including sorafenib, lenvatinib, or other anti-vascular endothelial growth factor inhibitor) before recruitment into this study.
7. Has a known additional malignancy that is progressing or requires active treatment. Exceptions include basal cell carcinoma of the skin, squamous cell carcinoma of the skin, indolent lymphomas, or in situ cervical cancer that has undergone potentially curative therapy
8. Has a history of prior solid organ transplants with or without any episodes of graft-versus-host disease.
9. Has a history of allogeneic bone marrow transplantation and peripheral stem cell rescue, with or without any episodes of graft-versus-host disease.

10. Has known extra-hepatic metastases.
11. Has known carcinomatous meningitis (also known as leptomeningeal carcinomatosis).
12. Has an active infection requiring intravenous systemic therapy or hospital admission.
13. Has a history or current evidence of any condition, therapy, or laboratory abnormality, including psychiatric or substance abuse disorder, that might confound the results of the trial, interfere with the subject's participation for the full duration of the trial, or is not in the best interest of the subject to participate, in the opinion of the treating investigator.
14. Is pregnant or breastfeeding, or expecting to conceive or father children within the projected duration of the trial, starting with the screening visit through 31 weeks after the last dose of trial treatment.
15. Untreated hepatitis B infection. Patients with chronic hepatitis B infection (defined as HBsAg positive) are eligible if they have started anti-viral therapy for at least 1 month and is continuing anti-viral treatment throughout the whole duration of this study.
16. Has experienced Grade 4 toxicity on treatment with prior radiation if done before.
17. Prior systemic therapy utilising an anti CTLA-4 or PD-1/PD-L1 agent or other forms of immunotherapy.
18. Has had prior radiation therapy (defined as  $> 0.5\text{Gy}$ ) to the area planning to be treated with SBRT.

## **4. STUDY TREATMENT**

### **4.1 Stereotactic Body Radiation Therapy (SBRT)**

Radical radiotherapy will be delivered by SBRT which is described as follows:

SBRT will be delivered by either a 10MV linear accelerator (TrueBeam, Varian Medical System, Palo Alto, USA) in the treating institution within 2 weeks of baseline investigations. Four-dimensional (4D) CT scanning for tracking the respiratory phases and radiation therapy planning is done with Real-time Patient Management (RPM) system (Varian Medical Systems, USA) or ExacTrac Adaptive Gating systems (Brainlab, AG, Germany) for motion detection. The gross tumor volume (GTV) with the co-registration of MRI and PET-CT images, and the motion of the tumor known as the internal target volume (ITV) are then contoured on the 4D CT images. The planning target volume (PTV) which encompasses the ITV with a 2–3mm margin, takes the set-up errors into account. Doses of SBRT range from 35Gy to 50Gy in 5 fractions over 5 to 14 days as adapted and modified from RTOG 1112 protocol, a phase 2 study investigating the use of sorafenib in combination with SBRT for inoperable HCC. The final dose is determined such that a maximum tumoricidal dose can be delivered to the tumors while the doses to the organs-at-risk are within the set tolerance

limits. Pretreatment positional verification by a cone-beam CT scanner, on-board imaging or other imaging devices available in each treating institution is done every time before SBRT with necessary correction if the linear and rotational displacement is more than 2mm and 2 degrees respectively. In addition, interval treatment verification with on-board x-ray imaging during SBRT may be performed additionally for identification of intra-fractional tumor displacement.

The details of target volume nomenclature and delineation as well as the acceptance criteria of SBRT are outlined in APPENDIX 1.

## **4.2 Concomitant therapy**

Prophylactic and/or rescue anti-emetics with aprepitant, 5-HT3 antagonists, metoclopramide as well as antacids, anti-H2 antagonists and proton pump inhibitors are allowed before, during and after SBRT as per local treating institution's protocols are allowed.

Other medication, which is considered necessary for the patient's safety and well being, may be given at the discretion of the investigator.

### **4.2.1 Dose Modification for SBRT**

SBRT should be withhold when grade  $\geq 3$  toxicity (based on CTCAE version 4.0) develops. It can be only be resumed if the toxicity returns to grade  $\leq 1$ .

If radiotherapy had to be interrupted more than 14 days because of toxicity or other reasons, the patient will be withdrawn from the study.

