## **5. DISCONTINUATION OF STUDY INTERVENTION AND PARTICIPANT WITHDRAWAL**

Discontinuation of treatment intervention dose not represent withdrawal from the study. As certain data on clinical events beyond study intervention discontinuation maybe important to the study, they must be collected through the participant's last scheduled follow-up, even if the participant has discontinued study intervention. Therefore, all participants who discontinue study intervention prior to completion of the protocol-specified treatment period will still continue to participate in the study for survival follow-up.

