### **5.1 Patient Discontinuation**

Patient have the right to voluntarily withdraw from the study at any time for any reason. In addition, the investigator has the right to withdraw a patient from the study at any time. Reasons for withdrawal from the study may include but are not limited to the following:

- 379 • Patient withdrawal of consent at any time
- 380 • Any medical condition that the investigator or sponsor determines may jeopardize the
- 381 patient's safety if he or she continues in the study
- 382 • Investigator or sponsor determines it is in the best interest of the patient
- 383 • Patient non-compliance

384 Every effort should be made to obtain information on patients who withdraw from the study.  
385 The primary reason for withdrawal from the study should be documented. However, patients  
386 will not be followed for any reason after consent has been withdrawn.

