## 409 **5.4 Withdrawal of Consent**

410 Patients are free to withdraw from the study at any time without prejudice to further  
411 treatment.

412 Patients who withdraw consent for further participation in the study will not receive SBRT (if  
413 not done), but will continue to be observed during future follow-up visits for progressive

disease and survival, which will continue until the end of the study unless the patient has expressly withdrawn their consent to survival follow-up. Note that the patient may be offered additional tests or tapering of treatment to withdraw safely.

A patient who withdraws consent will always be asked about the reason(s) for withdrawal and the presence of any adverse events (AEs). The Investigator will follow up AEs outside of the clinical study.

If a patient withdraws consent, they will be specifically asked if they are withdrawing consent to:

- all further participation in the study including any further follow up (e.g., survival contact telephone calls)
- withdrawal of consent to the use of their study generated data
- withdrawal to the use of any samples (if any)

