If progression is not confirmed, in the absence of significant clinical deterioration, then the patient should continue the study and on-treatment assessments until the next PD which will also require a follow-up confirmation scan. If the first PD is not confirmed by the immediate next scan, then the Investigator should not change the PD assessment of the first scan.

If a patient discontinues treatment (and/or receives a subsequent anticancer therapy) prior to radiologic progression, then the patient should still continue to be followed until confirmed objective disease progression.

Following confirmed progression, patients should continue to be followed up for survival every 2-3 months until death or until patient refusal.

Please refer to APPENDIX 4 and APPENDIX 5 for the definitions of objective response by RECIST 1.1, mRECIST, and PERCIST. The method of determination of metabolic tumor volume (MTV) and total lesion glycolysis (TLG) and total lesion activity (TLA) based on PET-CT scan with FDG and ACC respectively for subsequent exploratory statistical analyses were described in APPENDIX 5.

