### 903 (IV) Dose Specifications

904 The prescription isodose should encompass 95% of PTV. The dose to multiple PTVs within the  
905 same patient may vary. If there are multiple PTVs, each should be planned for one of the  
906 prescription doses listed above, with each specific covering isodose planned to encompass 95%  
907 of each PTV, with normalization to the PTV receiving the highest dose. The highest allowable  
908 doses to the target volumes that maintain normal tissue constraints should be used. A goal is that  
909 100% of the CTV is encompassed by the prescription dose. The unit of dose is Gy.  
910

911 Dose prescription is based on the volume of normal tissues irradiated (correlated with mean liver  
912 dose), as well as proximity of stomach, duodenum, small and large bowel (GI luminal structures)  
913 to the target volumes, as normal tissue constraints must be maintained in this study.  
914

915 In the absence of adjacent GI luminal structures that may limit dose, the PTV dose prescription  
916 should be as high as possible based on mean liver dose (MLD, defined as the mean dose to the  
917 liver minus all GTVs), with 4 potential dose levels: Use of effective liver volume (Veff) to aid in  
918 dose allocation is permitted but not mandatory. If there are discrepancies in the Veff and MLD  
919 for the prescription dose allocation, MLD has priority.

| Priority Constraint                       | Optional Constraint | Prescription Dose    |                                                             |
|-------------------------------------------|---------------------|----------------------|-------------------------------------------------------------|
| Mean liver dose
(liver minus all GTVs) | Liver Veff          | Planned prescription | If the maximum allowed MLD is exceeded at this planned dose |
| 13                                        | < 25%               | 50                   | Reduce to 45 Gy and re-evaluate                             |
| 15                                        | 25-29%              | 45                   | Reduce to 40 Gy and re-evaluate                             |
| 15                                        | 30-34%              | 40                   | Reduce to 35 Gy and re-evaluate                             |
| 15.5                                      | 35-44%              | 35                   | Do not treat; out of study                                  |

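### Section 4.2.1 withdraws patients from the study after a long SBRT interruption, while Sections 5, 5.2 and 6.5 keep patients who stop treatment in follow-up; 5.1 and 5.4 also disagree on follow-up after consent is withdrawn

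*Protocol*

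**What the plan says.** **After a long interruption.** Protocol Section 4.2.1 (Dose Modification for SBRT): "If radiotherapy had to be interrupted more than 14 days because of toxicity or other reasons, the patient will be withdrawn from the study".

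**After treatment stops.**
- Section 5, opening paragraph: "Discontinuation of treatment intervention dose not represent withdrawal from the study". It adds that participants who stop before completing the treatment period "will still continue to participate in the study for survival follow-up".
- Section 5.2 lists an adverse event that rules out further treatment as a reason to stop study treatment. It does not list it as a reason to leave the study.
- Section 6.5, on a patient who discontinues treatment before radiologic progression: "then the patient should still continue to be followed until confirmed objective disease progression". Survival follow-up comes after that.
- Section 6.8.5 takes it as given that a patient who stops treatment for a reason other than progression goes on having tumor assessments.

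**After withdrawal.**
- Section 5.1: "Every effort should be made to obtain information on patients who withdraw from the study". The same paragraph then says that patients "will not be followed for any reason after consent has been withdrawn".
- Section 5.4 says that patients who withdraw consent get no SBRT if it has not yet been given. The text runs "not done), but will continue to be observed during future follow-up visits for progressive" disease and survival, unless consent to survival follow-up is expressly withdrawn.

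**The concern.** Section 4.2.1 joins two decisions that the rest of the protocol keeps apart: ending SBRT and ending participation. It also ties the exit partly to toxicity. The same section withholds SBRT at grade 3 or higher and allows it to resume only at grade 1 or lower, so one direct route past 14 days is a severe toxicity that does not resolve. Loss to follow-up by that route may be informative.

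Best response, PFS, local control and OS all need assessments after treatment. If a site stops collecting them because it followed 4.2.1, no later analysis can recover them. That is why the conflict belongs in the protocol text and cannot be left to an analysis plan.

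The consent wording is a separate conflict. Sections 5.1 and 5.4 give a site opposite instructions about the same patient.

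**Working it through.** **1. Do the rules cover the same patient?** A patient withdrawn under 4.2.1 receives no further SBRT and has therefore stopped before completing the course. That is the group Section 5 describes.

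| Question about this patient | Section 4.2.1 | Other sections |
|---|---|---|
| Still in the study? | No | Yes (5; 5.2 treats an adverse event as ending treatment only) |
| Followed for survival? | Not if withdrawn | Yes (5; 6.5 after progression) |
| Tumor assessments continue? | Not if withdrawn | Yes, to confirmed progression (6.5; 6.8.5) |
| Triggering toxicity recorded? | Silent | Yes, from consent, and pursued after discontinuation (6.8.5) |

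Section 4.2.1 is the outlier on the first three rows. Section 5 alone secures survival follow-up only; progression follow-up rests on Section 6.5.

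**2. The plan's own figure.** Section 8 gives p0 = 0.60, p1 = 0.85, two-sided alpha 0.05, 80% power and n = 28. The normal approximation is

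n = [(1.960·√(0.60·0.40) + 0.842·√(0.85·0.15)) / 0.25]² = 25.4, so 26.

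With a continuity correction it is 29.3, so 30. The stated 28 lies between. Dropout: 28 / (1 − 0.20) = 35, as stated. The textual conflict does not depend on these figures; they set the scale for what follows.

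**3. Illustration of size.** Assumptions, none of them in the protocol: 28 patients start SBRT, 3 are withdrawn, all 3 are non-responders, and all 3 leave the denominator. The intervals are exact (Clopper-Pearson) 95%; the tail is P(X ≥ x) at a response rate of 0.60, to be compared with 0.025.

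| Responders | All 28: interval (tail) | 25 left: interval (tail) | Verdict against 60% |
|---|---|---|---|
| 20 | 51.3–86.8% (0.1485) | 59.3–93.2% (0.0294) | fails both ways |
| 21 | 55.1–89.3% (0.0740) | 63.9–95.5% (0.0095) | changes |
| 22 | 59.0–91.7% (0.0315) | 68.8–97.5% (0.0024) | changes |
| 23 | 63.1–93.9% (0.0111) | 74.0–99.0% (0.0004) | passes both ways |

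The verdict changes only at 21 or 22 responders. The planned rate of 85% implies 0.85 × 28 = 23.8 responders, just above that window.

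**4. Range over the unknown number withdrawn.** Suppose the true rate over all 28 is 60% and the k withdrawn are all non-responders. The rate among those left is then 16.8 / (28 − k). The last column is the binomial chance, at that rate, of reaching the exact upper-tail 0.025 threshold for 28 − k patients.

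| k | Rate among those left | Threshold | Chance of passing |
|---|---|---|---|
| 0 | 60.0% | 23/28 | 0.011 |
| 1 | 62.2% | 22/27 | 0.027 |
| 2 | 64.6% | 21/26 | 0.060 |
| 3 | 67.2% | 21/25 | 0.052 |
| 4 | 70.0% | 20/24 | 0.111 |
| 5 | 73.0% | 19/23 | 0.217 |

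If all 28 stay in the denominator with the withdrawn counted as non-responders, the threshold stays at 23/28 and there is no inflation.

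**5. Consent.** Section 5.1 ends all follow-up once consent is withdrawn. Section 5.4 continues observation by default and ends it only if the patient expressly declines survival follow-up. A patient who withdraws consent without saying more is treated differently under each.

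**The case against.** The strongest reply is that one sentence in a dose-modification section stands against several that point the other way. Section 5.1 lets the investigator withdraw a patient, asks for every effort to obtain information on those who leave, and ends follow-up only when consent is withdrawn. A sensible site might keep following the patient. The trigger is also narrow: more than 14 days, in a five-fraction course planned over 5 to 14 days. This lowers the likely number of patients but does not tell the site which sentence governs.

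A reader might infer more than the protocol supports:

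- *That the worst outcomes vanish from every endpoint.* No text excludes withdrawn patients from analysis. Section 2.4 says the 28 recruited will be analysed, and analysis sets are commonly left to an analysis plan.
- *That toxicity is understated as a matter of rule.* Section 6.8.5 collects adverse events from consent and pursues them after discontinuation, so the toxicity behind the interruption is on record. Only late toxicity arising afterwards is at risk.
- *That these patients are the non-responders, or that all leave because of toxicity.* The rule also covers other reasons, no outcomes are given for them, and some will have had part of the dose.
- *That the dose table in Appendix 1 (IV), which puts some patients out of the study, adds to the problem.* It concerns patients who never start SBRT.

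On consent, Section 5.4 offers graded withdrawal and asks specifically about use of data, and 5.1 could be read as meaning full withdrawal only. That softens the conflict, but 5.1 does not say so.

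**Conclusion.** The contradiction is real and lies in operative text. Section 4.2.1 cannot be followed together with Sections 5, 5.2 and 6.5 and the premise in 6.8.5. Applied literally, it permits a loss of later response, PFS, local control, OS and late-toxicity data that is partly related to toxicity. This is a risk created by the wording. It is not a stated exclusion.

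The size is unknown, because the protocol gives no withdrawal rate. With 28 patients each is 3.6% of the total (1/28), so a few matter. The figures above are upper-end illustrations: they assume that every withdrawn patient is a non-responder and leaves the denominator. The three-patient example decides the result only at 21 or 22 responders.

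The conflict between Sections 5.1 and 5.4 also stands, as a separate and smaller drafting point.

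**What to change.** 1. Reconcile Section 4.2.1 with Sections 5, 5.2 and 6.5 by separating the end of SBRT from the end of follow-up. Leave the interruption rule itself unchanged.
2. State that patients whose SBRT ends in this way stay in progression follow-up as in Section 6.5 and in survival follow-up as in Section 5. Cite both, since Section 5 alone does not cover progression.
3. State that every patient who starts SBRT stays in the denominator.
4. Separately, make Sections 5.1 and 5.4 give one rule on what is observed after consent is withdrawn, using the graded choices already listed in 5.4.

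The cost is a protocol wording change and a few more follow-up visits for the patients affected. The reported response rate may look slightly less favourable.
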